## 1 Background

While breastfeeding initiation rates are high in Ontario, duration and exclusivity rates drop precipitously in the first weeks and months after birth. Despite being above the national average, Ottawa breastfeeding rates are still low, with 56.3% of women exclusively breastfeeding shortly after birth, down to 39.1% at 6 months according to an Infant Care Survey. In Canada, the exclusive breastfeeding rate at 6 months, the widely accepted ideal standard to achieve, was reported to be 14.1% in the Canadian Maternity Experience Survey. Breastfeeding confers a multitude of long-term infant and maternal health benefits, with the potential for major economic gains. Studies have shown that each additional month of exclusive breastfeeding can lead to a 30% decrease in infection-related hospitalizations in the first few months of life. Also, formula-fed healthy infants experience a three times higher risk for developing severe respiratory illness when compared to infants exclusively breastfed for 4 months. Moreover, breastfeeding duration during infancy was found to be inversely proportional to the risk of being overweight in childhood. For mothers, breastfeeding decreases the risk of breast and ovarian cancers. Also, an inverse relationship between maternal depressive symptoms and breastfeeding has been shown. Therefore, health dollars invested in supporting and promoting exclusive breastfeeding have the potential to yield a high rate of return in preventing acute and chronic illnesses. Low breastfeeding self-efficacy, insufficient knowledge, skills and support, and breastfeeding problems that lead to inadequate milk supply are associated with early weaning. If these modifiable factors can be addressed early and consistently through support from lactation experts, the likelihood increases that a woman will breastfeed longer and more exclusively. By providing mothers with breastfeeding support, tools and techniques, their confidence in their ability to breastfeed will increase, with direct positive repercussions on exclusive breastfeeding duration.

Breastfeeding support strategies that rely on face-to-face interventions are more likely to succeed than support offered reactively, as per a recent systematic review. Women should be offered ongoing opportunities to receive advice through scheduled visits so as to ensure support availability. Unfortunately, comprehensive breastfeeding support is not widely available for many women, leading to unidentified breastfeeding difficulties. These difficulties can result in longer hospital stays and early hospital readmissions, because of their association with conditions such as neonatal jaundice, dehydration and poor weight gain. These neonatal concerns could, however, be addressed comprehensively in a community setting (and not in the hospital), resulting in a decrease in prolonged hospital stay and hospital readmissions. However, little is known about the most effective way to support and manage early postpartum issues, particularly jaundice, in the community.

We have received funding from the Ontario Ministry of Health and Long-Term Care to evaluate the efficacy and cost effectiveness of a breastfeeding/jaundice clinic based in the community after early discharge from the hospital. This multidisciplinary community clinic, developed in partnership between the research team, the Ottawa Hospital, and Public Health, will provide a comprehensive support for breastfeeding mothers during the first month after delivery. Open six days a week, the clinic will be staffed by family physicians (FP), Registered Nurses (RN), both health care providers with maternal/newborn experience, and Public Health Nurses (PHN)/lactation consultants (LC), to provide an initial assessment within 12 to 48 hours after hospital discharge and then follow-up breastfeeding consultations as needed during the first month after discharge. FP will be available each morning to do

an assessment of the infants and the mothers who are attending the clinic. The clinic will only enroll eligible women willing to participate in a research project to evaluate this new program, in order to assess whether early discharge with the support of this type of program in the community really helps breastfeeding mothers and their babies in transitioning from the hospital to home. The funding will support: 1) 1.0 FTE PHN/LC and 1.0 FTE RN on site, 2) the research infrastructure for a randomized controlled trial comparing the percentage of exclusive breastfeeding at 3 months and other secondary outcomes, between 2 groups of participants recruited at the Ottawa Hospital (e.g., women receiving the current standard of care and women accessing the services of the post-partum clinic).

The objective of the BEST ABCs trial will be to explore a new model for post-partum transition by offering women and their infants postpartum support in a multidisciplinary clinic. This clinic will address three important themes described in the literature: improving duration and rate of exclusive breastfeeding, preventing costly postnatal (maternal and neonatal) problems (e.g. the interrelated issues of jaundice and breastfeeding difficulties), and determining benefits associated with shorter hospital stays. For families that have challenges accessing services, even small problems can quickly manifest into difficulties leading to breastfeeding cessation, emergency room visits, and costly readmissions. The proposed community clinic will address early postpartum maternal newborn problems, move care away from hospitals when feasible and safe, and enhance health care system value. We will evaluate patient outcomes, mother satisfaction, and the costs associated with this new model. If successful, this model could be tested throughout Ontario.

We are currently conducting a pilot study (Phase 1) at The Ottawa Hospital over 3 months before the beginning of the BEST ABCs trial (Phase 2) to assess the feasibility of recruiting women and to test the data collection tools that we have developed and will be using for the RCT. We are collecting information on the current experience of breastfeeding women in the Ottawa region and their use of existing resources to provide a baseline estimate of the outcome rates.

## **2 Aim of Study and Study Design**

### **2.1 Study Objectives**

We will enroll women meeting the inclusion and exclusion criteria for the trial. The objectives of this study are to:

1. Determine if care provided through this community based postpartum clinic can improve duration and rate of exclusive breastfeeding, prevent costly postnatal problems and reduce length of hospital stay and the number of readmissions for new mothers.
2. Determine the level of satisfaction of the mothers attending this clinic with the care they received.
3. Determine the cost effectiveness of the new clinic and what the costs are associated with implementing a community-based postpartum clinic.
4. Determine the feasibility of operating this type of clinic in other settings across Ontario.

## 2.2 Hypothesis

We hypothesize that women discharged within 24 ( $\pm 12$ ) hours post vaginal delivery or 48 ( $\pm 12$ ) hours post-Caesarian section) and referred to the post-partum clinic will show a higher rate of exclusive breastfeeding at 3 months post-delivery than those who do not participate in this follow-up program (women from this study and from the previous pilot study). Our secondary hypothesis relates to the use of resources and the economic impact of the clinic. We believe that there will be fewer neonatal emergency room visits, fewer hospital readmissions and an overall decrease in the use of hospital and healthcare resources from the new mothers attending the breastfeeding clinic. This will lower the costs associated with these resources and help increase bed availability at hospitals and medical centers. We also hypothesize that women attending the clinic will be more satisfied and that the sustainability of this clinic and transferability to other settings will be feasible.

## 2.3 Primary Outcome

- The rate of exclusive breastfeeding at 3 months post-birth. We define exclusive breastfeeding as the feeding of the infant's mother's milk only for at least 2 weeks prior to collected outcome.

## 2.4 Secondary Outcomes

1. Rates of hyperbilirubinemia requiring phototherapy or hospitalization
2. Poor infant weight gain requiring intervention (pumping, supplementation, hospitalization)
3. Incidence of breastfeeding difficulties (e.g., sore nipples, insufficient milk supply, inadequate latch, engorgement)
4. Breastfeeding self efficacy score (Breastfeeding Self Efficacy Scale or BSES) at 2 weeks, 1 month and 3 months
5. Score of the Edinburgh Post-partum Depression Scale for new mothers
6. Access to community-based services: Public Health Clinics, Family Doctor, Pediatrician
7. Number of emergency department visits for the mother and the baby
8. Number of hospital readmissions for the mother and her baby
9. Mothers' satisfaction with the support received
10. Length of stay in the hospital, from delivery to discharge
11. Costs associated with this community-based postpartum clinic.

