### **3.4 Intervention arm post-discharge events**

Women randomly assigned to the intervention will be discharged approximately 24 hours following a vaginal delivery or approximately 48 hours following a C-section. While this is the aimed ideal time of discharge, there may be variation as time of discharge will ultimately depend on the attending physician/midwife's opinion/orders and what he/she feels is in the best interest of the mother and her newborn. Women who choose to stay in the hospital longer will still be referred to the Monarch Clinic and will not be excluded from the study.

Women and their infants will be expected to attend a pre-booked appointment at the breastfeeding clinic, scheduled within 48 hours of their discharge. Clinic staff will follow up with the participant if she fails to keep the mandatory follow-up appointment. This first appointment will include maternal assessment and care (e.g., wound care, prescriptions), neonatal care (e.g., tongue-tie clips, jaundice screening using transcutaneous bilirubinometer), blood work including TSB (samples couriered to TOH central laboratory, HBHC postpartum assessment, and breastfeeding assessment and support. Family physicians will be available for on-site consultations in the mornings, and lactation consultants and registered nurses will be at the clinic throughout the day from Monday to Friday and Saturday mornings. Medical data (e.g., bilirubin level (transcutaneous and serum), newborn assessment, infant weight gain, urination and defecation frequency, breastfeeding assessment and progress, maternal care) found in the clinic chart will be gathered.

The Bilirubin Pathway, established by the CMNRP, will be used to guide for the management of neonatal jaundice. Those guidelines provide recommendation for subsequent TSB and or TCB follow-up, according to the modified Buthani's normogram and whether risk factors for hyperbilirubinemia are

present or not. For babies discharged before 24 hours, blood for the newborn screening will be drawn at the first visit and sent by mail to the Newborn Screening Ontario laboratory located at CHEO.

Additional follow-up visits at the breastfeeding clinic will be made available to participants for the month following the birth of their baby.

Participants in the intervention group will also be contacted at 2 weeks, 1 month and 3 months to complete the different surveys and questionnaires (3.5).

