| Maternal care and neonatal care (jaundice screening using transcutaneous bilirubinometer and weight gain assessment) at the clinic. |   | X |   |     |     |     |     |     |
| Breastfeeding support at clinic                                                                                                     |   | X | X |     |     |     |     |     |
| Additional medical care at clinic                                                                                                   |   |   | X |     |     |     |     |     |
| Collection of medical data from visits at clinic                                                                                    |   | X | X |     |     |     |     |     |
| Demographics survey                                                                                                                 |   |   |   |     |     | X S |     |     |
| Edinburgh Postnatal Depression Scale                                                                                                |   |   |   |     | X S | X S |     |     |
| Breastfeeding local complications survey                                                                                            |   |   |   | X S |     | X S |     |     |
| Breastfeeding survey                                                                                                                |   |   |   | X S |     | X S | X S |     |
| Use of resources survey                                                                                                             |   |   |   | X S |     | X S | X S |     |
| Self-efficacy survey                                                                                                                |   |   |   | X S |     | X S | X S |     |
| Mother Satisfaction Survey                                                                                                          |   |   |   |     |     |     | X S |     |
| 6 month follow up survey                                                                                                            |   |   |   |     |     |     |     | X S |

Index: X = Women assigned to the breastfeeding clinic program will be completing these events

S = Women assigned to the standard care will be completing these events

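### Secondary outcome 2 counts poor weight gain only once it is recognised and acted on, and scheduled assessment after discharge is described for the clinic arm only, so the comparison partly measures who was assessed and treated

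*Protocol*

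**What the plan says.** Section 2.4 gives secondary outcome 2 as "Poor infant weight gain requiring intervention (pumping, supplementation, hospitalization". The protocol states no weight, percentage loss, weighing age or criterion for needing intervention.

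The Background (section 1) names difficulties with an "association with conditions such as neonatal jaundice, dehydration and poor weight gain" and continues: "These neonatal concerns could, however, be addressed comprehensively in a community setting (and not in the hospital".

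For the clinic arm, section 3.4 books a first visit within 48 hours of discharge, with staff follow-up if it is missed. Its content includes "HBHC postpartum assessment, and breastfeeding assessment and support". Further visits are available for a month. Clinic-chart data are abstracted: "newborn assessment, infant weight gain, urination and defecation frequency, breastfeeding assessment and progress, maternal care) found in the clinic chart will be gathered".

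The calendar (section 3.8) has a row for "Maternal care and neonatal care (jaundice screening using transcutaneous bilirubinometer and weight gain assessment) at the clinic". It carries an X and no S, and the key reads "X = Women assigned to the breastfeeding clinic program will be completing these events". The row for collecting medical data from clinic visits is also X only.

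Control mothers (section 3.3) may use existing community care but not the study clinic. Data described for both arms are hospital-chart items up to discharge, including supplementation (section 3.2.1), and the mothers' surveys (section 3.5), which ask about infant readmission.

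Section 4.3 takes secondary outcomes from medical data entered by research staff and compares arms with chi-squared, t or Fisher tests.

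**The concern.** The event has two parts: poor gain, and an intervention for it. Both depend on someone weighing the infant, forming a judgement and acting. Assignment to the clinic changes how likely that is, because it brings a scheduled assessment with staff on hand. It may also change which action is taken.

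The three qualifying actions are scored alike. If the clinic turned a hospitalization into a spell of pumping, it would have moved care in the direction the Background wants, yet the infant would still count as one event. An infant whose slow gain is noticed only because of a clinic visit adds an event with no counterpart among controls.

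Preventing costly postnatal problems is part of Objective 1. A difference on this outcome could be read as harm or benefit when growth is the same, and a real benefit could be hidden.

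**Working it through.** The protocol gives no rate, effect size or power for this outcome, so there is no stated figure to reproduce. The check has two parts.

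**1. Who can become an event, and where it would be recorded**

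| Step | Clinic arm | Control arm |
|---|---|---|
| Scheduled weight-gain assessment after discharge | Yes (3.8, X) | None described (no S) |
| Breastfeeding support visit | Pre-booked, missed visits followed up (3.4) | Existing community care (3.3) |
| Post-discharge chart abstracted | Clinic chart (3.4) | None described |
| Hospital chart to discharge | Yes (3.2.1) | Yes (3.2.1) |
| Mothers' surveys | Yes (3.5) | Yes (3.5) |

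Only the last two rows are common, and the hospital chart stops at discharge.

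**2. Size of a difference with equal growth (illustration)**

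Inputs:
- Planned arm sizes are 306 clinic and 154 control, with 15% attrition (section 4.1). Evaluable: 306 × 0.85 = 260 and 154 × 0.85 = 131.
- Assumed: true poor gain g = 10% in both arms.
- Assumed: d is the chance that a poor gainer is recognised and treated.
- Assumed: two-sided 5% test, since section 4.3 does not state sidedness for secondary outcomes.

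Formulas:
- Observed rate p = g × d, so RR = d(clinic) / d(control). The true rate g cancels.
- Pooled rate P = (131 p_control + 260 p_clinic) / 391.
- se0 = √[P(1 − P)(1/131 + 1/260)]
- se1 = √[p_control(1 − p_control)/131 + p_clinic(1 − p_clinic)/260]
- Chance of significance ≈ Φ[(|difference| − 1.96 se0) / se1], plus the small opposite tail.

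Worked case, 50% control against 90% clinic:
- Rates are 0.10 × 0.50 = 5% and 0.10 × 0.90 = 9%, so the difference is 0.04.
- P = (6.55 + 23.4) / 391 = 0.0766; se0 = 0.0285; se1 = 0.0260.
- (0.04 − 1.96 × 0.0285) / 0.0260 = −0.61, so Φ ≈ 0.27.

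| d control | d clinic | Observed rates | RR | Chance of p < 0.05 |
|---|---|---|---|---|
| 50% | 50% | 5% vs 5% | 1.0 | 5% (nominal) |
| 50% | 70% | 5% vs 7% | 1.4 | about 11% |
| 50% | 90% | 5% vs 9% | 1.8 | about 27% |
| 30% | 90% | 3% vs 9% | 3.0 | about 61% |
| 90% | 50% | 9% vs 5% | 0.56 | about 35% |

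Simulating the chi-squared test gives 10%, 27%, 63% and 34% for the four unequal rows. For 50% against 90%, the chance is about 14% if g is 5% and about 55% if g is 20%.

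**The case against.** **The event requires poor gain.** On the literal wording, pumping or supplementing a normally growing infant is not an event. This stands. A reader might infer that all clinic advice to pump inflates the outcome, and so add points to the clinic rate on top of true need. The definition does not support that: unless normal infants are labelled poor gainers, the rate cannot exceed the rate of poor gain. The illustration keeps to that limit.

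**The clinic need not look worse.** This also stands. A reader might infer that the outcome will make the clinic appear harmful. The trial aims to raise exclusive breastfeeding, so clinic staff may avoid supplementation while less-supported controls use it more. The last row of the table shows the reverse result. The protocol does not list pumping or supplementation among clinic services, so that the clinic starts them is an inference from the Background and sections 3.4 and 3.8.

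**Controls are not without care.** Section 3.3 leaves them their family doctor, public health unit or private services, and does not say routine weighing is absent. This narrows the gap in recognition by an unknown amount. It does not make assessment equal.

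**Detail may sit elsewhere.** The questionnaires in section 8 are listed by title only, and no analysis plan is shown. A common survey item or a weight threshold may exist. A common item would equalise recording, but an infant would still have to be recognised and treated before there was anything to report.

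**It is one of eleven secondary outcomes.** True, and emergency visits and readmissions are covered by outcomes 7 and 8. This limits the weight of the point.

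**Conclusion.** The concern holds as an ascertainment problem in one secondary outcome. As written, the between-arm comparison mixes infant growth with how often poor gain was recognised and treated, and the plan describes scheduled recognition in one arm only. With equal growth, the assumed scenarios give risk ratios from 0.56 to 3.0 and a chance of a significant result of about 11% to 61%, against a nominal 5%. These figures rest on the assumed 10% poor-gain rate and the assumed recognition rates, neither of which the protocol supplies. They show what could happen and do not predict it. The direction is open. The primary outcome is not touched, so the point is minor to moderate.

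**What to change.** In section 2.4, split secondary outcome 2 into its components.

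- **Compared between arms:** hospitalization for poor weight gain, ascertained by the same survey item in both arms and not from the clinic chart. The surveys at 2 weeks, 1 month and 3 months already ask about infant readmission, so a reason could be added there if it is not already asked.
- **Reported by arm without a test of benefit or harm:** pumping and supplementation for poor gain, labelled as process of care, with a note that assessment was unequal.

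The cost is rewording one outcome and, at most, one survey item. The compared component will have fewer events and a wider interval, and it overlaps with outcome 8 (readmissions). Some dependence on detection remains, because a clinic visit can itself lead to a hospitalization, although averting one is an effect the trial wants to see. Defining poor gain by weight measured at a fixed age in the same way in both arms would remove more of the bias, but it needs a new visit or record request for controls.

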## 2.5 Inclusion criteria:

Mothers having delivered a baby at The Ottawa Hospital - General or Civic Campus:

1. Who are  $\geq 18$  years at the time of enrollment
2. Who are any parity, with a singleton infant born  $> 36 + 6$  weeks of Gestational Age
3. Who have no medical counter indication for discharge at 24 ( $\pm 12$ ) hours post vaginal delivery or 48 ( $\pm 12$ ) hours post C-section delivery and for which the physician (family physician or obstetrician) has agreed that the mother is eligible
4. Who are breastfeeding and intend to breastfeed their baby upon discharge
5. Whose infant is healthy with no counter indication for discharge at 24 ( $\pm 12$ ) hours post vaginal birth or 48 ( $\pm 12$ ) hours post C-section birth and for which the physician (family physician or paediatrician) has agreed that the infant is eligible
6. Who can be contacted by phone or E-mail after hospital discharge

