## 2.6 Exclusion criteria:

Mothers:

1. Who have had breast surgery
2. Who do not understand French or English
3. Who are unable to present to the clinic (transport not available)
4. Who have birthed multiples or preterm
5. Whose infants are exclusively formula-fed
6. Who are adoptive mothers
7. Who have been identified with a psychological risk that may impede her ability to attend the first appointment at the clinic

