### 3.2 Events prior to hospital discharge

#### 3.2.1 Data collection

Once consent has been obtained, the research team will collect information about delivery (mode of delivery and date and time of birth), obstetrical (previous pregnancies, parity) history, and information on the baby (gender, ethnicity, gestational age at birth, birth weight, Apgar score, bilirubin levels (TCB [trans cutaneous bilirubin] and/or TSB [total serum bilirubin], whether supplementation was given and date and time of discharge) from the hospital chart.

Contact information will be recorded in the study master log. As well, the OHIP number will be recorded in the master log to eventually allow the linkage of the dataset to ICES administrative data.

Upon confirmation by the pediatrician, the obstetrician, the family physician, and/or the midwife in attendance that the mother and baby have no counter-indication for early discharge, the research team will proceed to randomize the participant.

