#### 3.2.2 Randomization

Study participants will be randomly assigned to either the intervention (discharge with follow-up at the breastfeeding clinic) or the control (standard of care) groups via a 2:1 allocation ratio, with group designations being determined after the patient is enrolled and informed consent is obtained. Stratification will be used to improve allocation balance by site of recruitment and parity of participants. Group designation is given from a randomization list, which will be generated using a permuted randomized block design, with permuted blocks of sizes 3, 6, and 9 units, prior to study initiation. This list is then entered directly into REDCap's group allocation component which assigns group placement based on the inputted randomization list at the time of initial data entry, all the while blinding the study researchers, recruiters, and participants to the randomization allocations prior to patient enrollment and data collection. The study staff will then inform the participant of their randomization group. Rather than occurring at the time of consent, randomization will be delayed until confirmation by the nurses and/or attending physicians that the participant is indeed a candidate for discharge at approximately 24h ( $\pm$  12) after vaginal or 48h ( $\pm$  12) after C section delivery.

[figure not shown]

**FIGURE 1. Schematic diagram showing the two possible outcomes after randomization.** In the case of this breastfeeding study, the participants may be assigned the standard-care or the post-partum clinic option.

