### 4.3 Statistical analysis

All outcomes will be analyzed based on the intention-to-treat principle, in accordance with the randomization allocations described previously. The primary goal of this study is to test the hypothesis that rates of exclusive breastfeeding at 3 months (defined as the feeding of only the infant's mother's milk for at least 2 weeks prior to collected outcome) will be higher in the group of women attending the post-partum clinic, as compared to those under standard of care. For comparison between intervention and control arms we will employ a generalized estimating equation multivariable regression model to account for prognostic risk factors that have not been sufficiently balanced by randomization. Group and individual level covariates will be included in the model, with recruitment site as the clustering unit to allow for inference at the individual level. This design will also investigate the effect of demographic

drivers such as maternal age, education, parity, etc., on the primary outcome, producing both crude and adjusted risk estimates and their 95% confidence intervals.

Secondary outcomes will be collected by studying the medical data (such as rates of hyperbilirubinemia and self-efficacy) that will be entered in the database by the research staff. This data will be compared across case and control groups using the Pearson Chi-squared, Student's t, or Fisher's exact test, depending on their observed frequencies. We will also compare the statistics and outcomes from the present study with baseline estimates from phase 1. The answers women provide through their questionnaires and surveys will be the main instruments for determining exclusive breastfeeding rates and their behavioral and emotional measurements. For the cost-effectiveness analysis, direct and indirect costs for the intervention and control groups will be compared regarding use of resources (e.g., clinic visits, physician visits, Emergency Department visits, hospital readmission, and indirect cost).

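### Feeding status at randomisation, a probable strong predictor of the primary outcome, is neither stratified on nor fixed in the primary model, and the chart item that could supply it has no cut-off at randomisation

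*Protocol*

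**What the plan says.** **Eligibility.** Section 2.5, criterion 4, admits mothers "Who are breastfeeding and intend to breastfeed their baby upon discharge". The matching exclusion in section 2.6, criterion 5, is "Whose infants are exclusively formula-fed". Partly formula-fed infants fall between the two and are eligible.

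**Primary outcome.** Section 2.3, measured at 3 months: "We define exclusive breastfeeding as the feeding of the infant's mother's milk only for at least 2 weeks prior to collected outcome".

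**Allocation.** Section 3.2.2: "Stratification will be used to improve allocation balance by site of recruitment and parity of participants". No other factor is named.

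**Primary model.** Section 4.3 uses a multivariable generalised estimating equation model "to account for prognostic risk factors that have not been sufficiently balanced by randomization". It also says that the effects of mother's age, education and parity will be examined, in an open-ended list, and that crude and adjusted estimates will be produced. Feeding status at entry is not named.

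**Chart data.** Section 3.2.1 abstracts, among the infant items, "whether supplementation was given and date and time of discharge". No time limit is set for supplementation.

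**The concern.** Whether an infant is receiving only mother's milk when the mother is randomised is the nearest thing at entry to what is measured at 3 months. An infant still mixed-fed at discharge has to move to exclusive feeding before the outcome can be met; an exclusively fed infant only has to continue. Success rates are therefore likely to differ between the two groups.

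Two things in the protocol stop this information from being used well.

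- **The adjustment rule.** Covariates enter because they look imbalanced, not because they predict the outcome. A strong predictor that happens to be balanced can be left out, and the final model depends on a judgement made after the data are seen.
- **The timing of the chart item.** Randomisation precedes discharge, and discharge timing is part of what differs by arm: about 24 or 48 hours in the intervention arm (3.4), current hospital practice in the control arm (3.3). If supplementation is abstracted over the whole stay, it may include feeds given after allocation, over stays of different length. An arm difference produced in that way could itself look like imbalance and trigger adjustment for a post-randomisation variable.

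At stake are some precision in the primary comparison and the credibility of a pre-specified primary model.

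**Working it through.** **Inputs from the protocol**
- Control rate 50%; randomised numbers 154 control and 306 intervention; attrition 15% (4.1).
- Analysed numbers after attrition: 154 × 0.85 ≈ 131 and 306 × 0.85 ≈ 260.
- Local context: "56.3% of women exclusively breastfeeding shortly after birth" (section 1). The complement, 43.7%, includes formula-only infants, so it exceeds the mixed-fed share and serves only to show that this share need not be small.

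**Inputs assumed, because the protocol gives neither**
- s, the share of randomised infants supplemented before randomisation: 20–40%, widened to 10–40% below.
- d, the gap in the 3-month exclusive rate between the two feeding groups: 20–40 points.

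**The plan's own figure.** Section 4.1 gives 200 per group for a 15% relative difference, one-sided 0.05. Its 0.9 is printed as β and read here as power. A relative 15% (50% vs 57.5%) needs 756 per group. An absolute 15 points (50% vs 65%) needs 185, or 198 with continuity correction, which matches 200. That discrepancy is a separate matter, but it is why power is shown under both readings.

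**Formulas**
- Outcome variance explained = s(1−s)d² / 0.25, where 0.25 = 0.5 × 0.5.
- SD of the chance imbalance = √[s(1−s)(1/306 + 1/154)] = √[s(1−s)] × 0.0988.
- Shift in the crude risk difference = imbalance × d.

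**Results at 306/154 (shift in points for a 2-SD imbalance; variance explained in brackets)**

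| s | 2-SD imbalance | d = 20 | d = 30 | d = 40 |
|---|---|---|---|---|
| 20% | 7.9 points | 1.6 (2.6%) | 2.4 (5.8%) | 3.2 (10.2%) |
| 30% | 9.1 points | 1.8 (3.4%) | 2.7 (7.6%) | 3.6 (13.4%) |
| 40% | 9.7 points | 1.9 (3.8%) | 2.9 (8.6%) | 3.9 (15.4%) |

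Worked cell: s = 0.3, d = 0.3 gives 0.21 × 0.09 / 0.25 = 7.6%. The imbalance is 2 × 0.4583 × 0.0988 = 9.1 points, and 9.1 × 0.3 = 2.7 points.

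**At 131/260, with s = 10–40%**
- Variance explained: about 1–15%.
- Chance of an arm imbalance of at least 5 points: 12–34%. Of at least 10 points: 0.2–6%.
- Shift at a 1.96-SD imbalance: 1.3–4.1 points.
- One-sided power, with the sample sizes divided by (1 − variance explained): from 0.886 to about 0.89–0.93 for 15 points absolute; from 0.41 to at most 0.45 for 15% relative.

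The power step treats adjustment as a proportional cut in variance on the risk-difference scale, which is an approximation.

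**Timing of the chart item.** Section 3.2.1 describes chart abstraction once consent is given and turns to randomisation afterwards, and the calendar in 3.8 places both in the Day 0 column. Yet the same list includes the time of discharge, which is not known at randomisation. The text fits either reading: supplementation recorded before allocation, or over the whole stay.

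**The case against.** **A covariate list belongs in the statistical analysis plan.** Largely true. The list in 4.3 is open-ended, feeding status could be added, and that plan is not at hand. But selection by observed imbalance is written into the protocol itself, and a missing time limit at data capture cannot be repaired later unless feeds before randomisation can be identified.

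**The effect is small and unbiased.** This stands. Allocation is random, so the expected bias is zero. At 306/154 and a 50% rate, the standard error of the crude difference is 0.5 × 0.0988, or 4.9 points, so even the largest shift in the table is less than one standard error and lies within what the confidence interval already allows for. Feeding status may also overlap with parity and education, so its added contribution could be smaller than shown.

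**Broad eligibility is right for this trial.** Also accepted. A clinic meant to help women with breastfeeding difficulties has good reason to admit those already supplementing.

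**Stronger readings that the protocol does not support**
- A reader might infer that supplemented women begin the trial already failing the primary outcome. They do not. The outcome is a 2-week look-back at 3 months, which no infant aged one or two days can pass or fail, and a baby supplemented in hospital can still meet it.
- A reader might take 43.7% as the share of mixed feeders in the trial. That figure comes from a general survey and includes formula-only infants, whom the trial excludes.
- A reader might conclude that the chart item is contaminated by feeds after allocation. The protocol leaves that possible but does not establish it, and it never proposes the item as a covariate.

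**Conclusion.** The point holds as a low-cost improvement to the primary analysis. It does not show that the comparison is biased or that the eligibility criteria are wrong. A probable strong predictor of the outcome is available from the chart, is not used in allocation, and would enter the primary model only through a data-dependent rule. The item as worded is not secured as a baseline measure.

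The benefit is a pre-specified model and a modest gain in precision: about 3–15% of outcome variance if 20–40% are supplemented and the gap is 20–40 points, falling to about 1% if only 10% are supplemented and the gap is 20 points. Confidence is highest in what the protocol says and in the weakness of imbalance-based selection. It is lowest in the size, because the share supplemented and the gap are both assumptions.

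**What to change.** Leave eligibility unchanged.

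- **Section 3.2.1:** restrict the supplementation item to feeds before the time of randomisation, recorded as one yes/no field: infant given only mother's milk from birth to randomisation.
- **Section 4.3:** name this field, together with site and parity, as fixed covariates in the primary model whatever the observed balance, in place of imbalance-based selection for these factors. Site now appears there as the clustering unit, so that sentence needs rewording at the same time.
- **Optional:** report the treatment effect within the two feeding groups as a pre-specified descriptive subgroup.

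The cost is one model degree of freedom for the feeding term, one sentence in 4.3, and a chart field that the abstractor must check against the randomisation time. It assumes that the chart shows when supplements were given.
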